#### *Confirming Eligibility: CRF*

A Clinical Record Form (CRF) will collect clinical data to confirm each patient meets the eligibility criteria. The researcher will work with the PCP at the end of each recruitment session to complete a CRF for all consenting patients. The CRF will record the following: patient's unique identifier for the study (allocated on consent), confirmed clinical diagnosis of OA hip and/or knee, age on day of consultation (<45 or 45 and older), and PCP's view on whether the patient is unable to consent or complete questionnaires (for example, because of severe mental illness, severe distress, very unwell generally, and difficulty reading or writing).

### **Recruitment and Consent Procedures for Filming Baseline Consultations (Pre-Randomization)**

Our preferred approach to seeking patient consent for filming baseline consultations is for the PCP to inform patients and take written consent at the start of the consultation. Consent will be itemised separately for (a) filming the consultation for the PCP to reflect on and (b) filming the consultation for the research team to analyse. To ensure patients have the necessary information to make a decision and the consent process is efficient we will give patients a participant information sheet before they go in to see the PCP. Our preferred approach to this is for reception staff to give a participant information sheet to all patients arriving with an appointment to see the participating PCP during a filming session. Patients will then be able to read the information in the waiting room before going in to see the PCP, depending on the variability in the time available as noted above.

The drawback to this approach is that some patients may arrive very close to their appointment time and, if the PCP is running to time, will not have very long to consider the information sheet. We will therefore be very clear that, if patients do consent, then they have the option to change their mind and withdraw consent without penalty by contacting the researchers at any time.

Furthermore, in this approach the onus is on the PCP for monitoring the numbers of patients consenting to be filmed, and maintaining awareness of when they have achieved the target of filming five consultations including at least one consultation regarding hip and/or knee OA.

If necessary (e.g., if recruitment using our preferred method is slow or the burden on PCPs is too high), we will try using two other procedures for seeking patient consent for filming consultations.

One, we will have a researcher present in the practice and reception staff will direct patients to talk to the researcher about the study. The researcher will talk the patient through the information sheet before they are called in to their appointment. The PCP will then take consent as described in

our preferred approach. This will make it easier for the research team to monitor consent and to notify the PCP when five consultations have been filmed (at least one for hip/knee OA).

Two, we will mail out participant information sheets with a cover letter approximately 1 week in advance to all patients booked in to see the PCP during a filming session. The PCP will then discuss the study and take consent as per our preferred approach outlined above. This has the advantage that patients will have longer to consider the request and will have time to contact the research team should they so desire. However, the major disadvantage of this procedure is that it would not be feasible for PCPs to do this in usual practice when undertaking EMPathicO training outside the context of a trial and so substantially reduces the likelihood and ease of ultimately rolling out our training for use as CPD by practicing PCPs.

The research team will review how long it takes to capture all the data required for PCP use during EMPathicO and for the researchers to have access to as part of the trial. We anticipate in particular it will be easier to capture the required “other” consultations than it will be to capture the OA consultation. We will ask the PCP to continue to seek consent to record consultations with patients consulting for hip and/or knee OA until one has been recorded with consent. We would like to try the following means of identifying such patients before proceeding with our preferred approach to consent outlined above.

- a) PCP to ask patients “what’s the main problem that you’re here for”.
- b) Reception staff to ascertain from patients checking in to see the relevant PCP whether they are coming for hip/knee OA, using the script in Box 1. Reception staff to offer potentially eligible patients the participant information sheet, then alert the PCP to proceed to seek consent.
- c) Questionnaire module on EMIS to ask patients when checking in to see the relevant PCP “what’s the main problem that you’re here for,” with fixed response options of “knee and/or hip pain / osteoarthritis” or “something else”. If knee and/or hip pain / OA, then EMIS to electronically notify the PCP.

## Outcomes

Table 2 lists all outcome and process measures for each group and time-point. We will explore using paper forms of the questionnaires and their equivalent online versions at the different measurement points. We will use Qualtrics as our online platform for questionnaires for patients, as it is specifically designed for collecting questionnaire data and therefore more suited to this than Lifeguide. We will use Lifeguide as our online platform for questionnaires for PCPs, as they will already be using Lifeguide to access the intervention (EMPathicO group) and/or instructions for filming consultations (all PCPs), and so it will be familiar to them and avoids the need to log on to a different system.

While in a future definitive trial we would want to collect data on healthcare utilisation, for example from a notes review, we are confident this is a reasonably standard process that can be managed successfully and is therefore not a priority for looking at in this feasibility trial. It is more important in this trial to assess the feasibility of our planned patient reported outcomes, process measures, and our more specialist need to record consultations.

**Table 2. Outcome and Process Measures**

| Construct                                           | Measure                                               | N items | Pre-intervention | Post-intervention | Pre-consultation | Post-consultation | Follow-up |
|-----------------------------------------------------|-------------------------------------------------------|---------|------------------|-------------------|------------------|-------------------|-----------|
| Patient Reported Outcome                     |                                                       |         |                  |                   |                  |                   |           |
| Pain intensity                                      | Numerical Rating Scale                                | 1       | -                | -                 | ALL              | -                 | ALL       |
| Symptoms                                            | Symptom change                                        | 1       | -                | -                 | -                | -                 | ALL       |
|                                                     | Symptom bothersomeness                                | 1       | -                | -                 | ALL              | -                 | ALL       |
| OA symptoms                                         | HOOS and KOOS                         |         | -                | -                 | OA               | -                 | OA        |
| Satisfaction with consultation                      | MISS for UK general practice             | 21      | -                | -                 | -                | ALL               | -         |
| Enablement                                          | Modified PEI                             |         | -                | -                 |                  | ALL               | ALL       |
| Health-related quality of life                      | SF-36                                    | 36      | -                | -                 | -                | ALL               | ALL       |
|                                                     | OR                                                    |         |                  |                   |                  |                   |           |
|                                                     | SF-12 v2                              | 12      | -                | -                 | -                | ALL               | ALL       |
| Wellbeing                                           | Short Warwick Edinburgh Wellbeing Scale  | 7       | -                | -                 | -                | ALL               | ALL       |
| Pain Medication Change                              | Bespoke Osteoarthritis Pain Medication Questionnaire  | 5       | -                | -                 | -                | -                 | ALL       |
| Adverse events                                      | Adverse events form                                   | 2       | -                | -                 | -                | -                 | ALL       |
| Patient Reported Process                     |                                                       |         |                  |                   |                  |                   |           |
| Perceptions of PCP empathy                          | CARE                                     | 10      | -                | -                 | -                | ALL               | -         |
| Anxiety                                             | HADS                                  | 14      | -                | -                 | -                | ALL               | -         |
| Perceptions of PCP response expectancies            | Bespoke item                                          | 1       | -                | -                 | -                | ALL               | -         |
| Response expectancies                               | Expectancy subscale of the CEQ           | 3       | -                | -                 | -                | ALL               | -         |
|                                                     | Treatment Expectation Questionnaire (TEX-Q)           | 11      | -                | -                 | -                | ALL               | -         |
| Treatment credibility                               | Credibility subscale of the CEQ          | 3       | -                | -                 | -                | ALL               | -         |
| Practitioner Reported Process                |                                                       |         |                  |                   |                  |                   |           |
| Self-efficacy for conveying empathy & optimism      | Bespoke self-efficacy scale                           | 8       | -                | PCP               |                  |                   |           |
| Outcome expectancy for conveying empathy & optimism | Bespoke outcome expectancy scale                      | 8       | -                | PCP               |                  |                   |           |
| Intentions to convey empathy & optimism             | Bespoke intentions scale                              | 4       | -                | PCP               |                  |                   |           |
| Directly Assessed Process                    |                                                       |         |                  |                   |                  |                   |           |
| PCP empathy behaviours                              | Filmed consultations                                  |         | RES              | RES               |                  |                   |           |
| PCP positive response expectancy statements         | Filmed consultations                                  |         | RES              | RES               |                  |                   |           |

|                        |                |  |  |     |  |  |  |
|------------------------|----------------|--|--|-----|--|--|--|
| PCP intervention usage | LifeGuide data |  |  | RES |  |  |  |
|------------------------|----------------|--|--|-----|--|--|--|

KEY: OA = completed by OA group only; ALL = completed by all patient participants; PCP = completed by primary care practitioner; RES = Researcher assessed.

### Timing and Modality

We will explore whether it is possible to assess patient-reported outcomes at pre-consultation baseline, as this will enable us to control for baseline statistically, making the final analyses more powerful. If we cannot find a feasible way of collecting pre-consultation baseline data then we will not propose doing this for the subsequent full trial.

The post-consultation measures will be assessed as soon as possible after the index consultation, ideally within 3 days. This is because effects on outcomes such as satisfaction with the consultation and patient enablement, and possibly also those outcomes capturing symptom perception, are likely to be immediate. It is also important to assess process measures related to the consultation (e.g. patient perception of PCP empathy) as soon as possible after the index consultation in order to reduce potential recall bias.

The follow-up time-point is two weeks after the index consultation. In a full trial we would anticipate wanting a longer follow-up period (e.g. 1-3 months, and even longer for health economic outcomes). However, we do not have time for this within our current funding. Furthermore, a 2-week follow-up still enables us to test the feasibility of collecting follow-up data directly from patients. This timing also allows us to collect some indicative data on early attrition which we can combine with insights from similar studies with longer follow-ups to estimate likely attrition rates for the full trial.

### Measures Completed by the OA Group

The patient-reported outcomes will differ slightly between the patients consulting for hip and/or knee OA and others, in order to ensure outcomes are as specific as possible, relevant to the patients, and map onto our logic model. For the OA sub-group, we have been guided by the recent publication of new OMERACT-OARSI core outcome domains for trials in hip and/or knee OA. This paper specifies that the following five core outcome domains must be measured: pain, physical function, quality of life, patient global assessment of the target joint, and adverse events including mortality. The follow-up paper, not due for 2 years, will recommend specific measures of each domain.

The short form of the Hip and Disability Osteoarthritis Score (HOOS-12) and the Knee Injury and Osteoarthritis Score (KOOS-12) are our candidate disease-specific primary outcome measures for hip and knee osteoarthritis. The HOOS-12 and the KOOS-12 each assess pain, function, and quality of life, and produce an overall summary hip/knee impact score respectively. We will use the brief 12-item formats, which demonstrate promising psychometric properties and reduced participant burden compared to the full 40-item versions. However, it is worth noting that the HOOS-12 and KOOS-12 were validated in patients undergoing joint replacement surgery and so it is important to explore their relevance to primary care patients in this feasibility study.

To assess the core outcome domain of patient global assessment of target joint, the OA group will be asked to complete the symptom change item for all-consulters modified for osteoarthritis. This asks patients to rate specifically their knee or hip symptoms now compared to two weeks ago.

A pain numerical rating scale will also be used in the OA sub-sample, as it is likely to be practically feasible for patients to complete a single-item pain score before a consultation; whereas completing

the 12-item HOOS or KOOS at a pre-consultation baseline would be more challenging, but we will explore whether it is feasible as part of this feasibility study.

Changes in osteoarthritis pain medication will be assessed using a bespoke Osteoarthritis Pain Medication Questionnaire. This instrument asks patients to list all the osteoarthritis pain medications they are using (to include all tablets, medicines, gels, and creams) and to rate whether and how, since starting the study, they have changed the amount that they use. In designing this instrument we drew on the design of the previously validated but complex Medication Change Questionnaire.

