### Patients:

Inclusion criteria all-consulters: Adults.

Inclusion criteria OA sub-sample: Consulting a participating PCP in relation to clinically diagnosed hip and/or knee OA, where OA is the only reason for consulting or one of two main reasons for consulting; minimum 45 years old (as per NICE guidance for OA).

Exclusion criteria: Patients who are unable to speak English, unable to consent or complete questionnaires (for example, because of severe mental illness, severe distress, very unwell generally, and difficulty reading or writing).

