## Measures Completed by All Participants

All patients will be asked to complete measures of symptoms, patient enablement, satisfaction, well-being, and quality of life as shown in Table 2.

We will explore the feasibility of two candidate primary outcomes that can apply to both OA consulters and others: symptom change, and symptom bothersomeness. The symptom change item asks patients to rate their overall symptoms now compared to two weeks ago, and was adapted from the COOP-WONCA charts. The symptom bothersomeness item asks patients to rate how bothersome their symptoms are, and was adapted from the item developed to assess severity of back pain in primary care. These are both single item generic measures, feasible to collect from a large number of patients with diverse health conditions. They add to the wellbeing and quality of life scales by specifically capturing patients' perceptions of symptoms.

The Patient Enablement Index (PEI) captures the extent to which patients feel confident and empowered by a consultation to cope with their illness, to keep healthy and to help themselves. The original publication described six items with 4 response options (much better/never/same or less/not applicable). Following other studies in the primary care and LifeGuide teams, we will modify the response scale to a 7-point agree-disagree Likert scale in order to increase sensitivity to change.

The Medical Interview Satisfaction Scale (MISS) measures patient satisfaction with the consultation and was used to detect post-intervention group differences in the Kepe Warm study. We have chosen the version of the MISS that has been specifically adapted and revalidated to be culturally appropriate for UK primary care. Patient satisfaction with the consultation is an important outcome for patients.

Patient wellbeing will be assessed using the Short Warwick Edinburgh Wellbeing Scale. The Warwick Edinburgh Wellbeing Scale underwent extensive development, focuses exclusively on positive aspects of wellbeing, and captures both hedonic and eudaimonic aspects of mental health. The short version is quicker to complete and retains robust psychometric properties as a unidimensional interval level scale.

For quality of life, we will use the SF-36

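### Symptom change is offered as a candidate primary outcome common to OA patients and others, but the protocol reads as giving OA patients a reworded item in its place

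*Protocol*

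**What the plan says.** Under Measures Completed by All Participants, the protocol proposes "two candidate primary outcomes that can apply to both OA consulters and others: symptom change, and symptom bothersomeness". It describes the first as follows: "The symptom change item asks patients to rate their overall symptoms now compared to two weeks ago". Of the pair it says: "These are both single item generic measures, feasible to collect from a large number of patients with diverse health conditions".

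Under Measures Completed by the OA Group, the same measure is changed. The stated purpose is "To assess the core outcome domain of patient global assessment of target joint", and for this "the OA group will be asked to complete the symptom change item for all-consulters modified for osteoarthritis". The content of the changed item is explicit: "This asks patients to rate specifically their knee or hip symptoms now compared to two weeks ago".

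Table 2 has one symptom change row, with one item, marked for all patients at follow-up only. There is no OA-only row for it, although HOOS/KOOS has one.

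The Patients inclusion criteria admit someone to the OA sub-sample "where OA is the only reason for consulting or one of two main reasons for consulting".

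The intended uses of the data are given elsewhere. Design describes a future trial in all-consulters with OA as a pre-planned sub-sample. Sample Size (Patients) justifies the numbers partly by the need to estimate the variance of the primary outcome. Planned Analysis says SDs and ICCs from this study will refine the full trial's sample size.

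**The concern.** An item cannot be both the generic measure shared by the two groups and a joint-specific measure in one of them. The two wordings need not agree in the same person. A patient who consults about a knee and about something else may report the knee as unchanged and overall symptoms as better, or the reverse. Symptom change has no pre-consultation score, because the comparison is built into the question, so no baseline value can be used to align the two versions afterwards.

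At stake is one of only two shared candidates. The third aim of the study is to finalise outcome measures. If OA patients see only the knee or hip wording, the study ends without knowing whether the overall item works in the patients for whom the training was mainly developed, and without an SD or ICC for that item that includes them.

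**Working it through.** **Does the OA version replace the generic item or add to it?**

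- For replacement: the OA item is described as the all-consulter item in modified form; it is introduced under a statement that outcomes differ slightly between the groups; Table 2 counts one item and has no OA row. Recruiting of Patients with OA and Others uses the term all-consulters for the patients capped at 6 per PCP, that is, the non-OA patients.
- For addition: Measures Completed by All Participants says every patient completes the symptom measures in Table 2, and the row is marked for all. Design uses all-consulters for the whole population.
- No sentence settles it. Replacement is the more natural reading, and a team following the OA section and Table 2 literally would issue one item to each patient.

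**Numbers affected**

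Inputs: up to 20 PCPs (Sample Size, Practitioners); 3 OA patients per PCP (Sample Size, Patients); 6 others per PCP (Recruiting of Patients with OA and Others).

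- OA: 20 × 3 = 60. Others: 20 × 6 = 120. Total: 60 + 120 = 180. This reproduces the protocol's 180 post-randomisation consultations under Directly Assessed.
- Share not answering the generic item under replacement: 60/180 = 33%.
- Patients answering it: at most 120 instead of 180. At the protocol's 80% completion target: 0.8 × 120 = 96 instead of 0.8 × 180 = 144.
- Over 10 practices, the average number per practice available for the ICC of the generic item falls from 180/10 = 18 to 120/10 = 12.

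**Effect on the precision of the SD**

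The 95% limits for the true SD relative to its estimate are √(df/χ²₀.₉₇₅) and √(df/χ²₀.₀₂₅), with df = n − 1. Clustering is ignored, which is an assumption; it would widen every interval.

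| Patients | n | Limits | n at 80% completion | Limits |
|---|---|---|---|---|
| All, one identical item | 180 | 0.906 to 1.116 | 144 | 0.896 to 1.131 |
| Others only, generic item | 120 | 0.887 to 1.145 | 96 | 0.876 to 1.166 |
| OA only, knee or hip item | 60 | 0.848 to 1.220 | 48 | 0.832 to 1.253 |

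At full numbers, the uncertainty in the SD of the generic item goes from about −9%/+12% to about −11%/+15%. That is modest. The larger loss is one of coverage: the 120 contain no OA patients, so the generic item's completion, acceptability and spread in that group are not observed at all.

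**The case against.** The strongest reply is that the difference is declared and reasoned. The OA section says outcomes will differ slightly so as to be specific and relevant, the knee or hip item serves a recognised core domain, and exploring measure options for OA consultations and others is itself an objective. All of that stands as a reason to have the joint-specific item. It does not explain why the same item is also called generic and common to both groups, and both aims can be met at once.

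Three stronger readings are tempting, and the documents do not support them.

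- A reader might infer that the protocol promises a pooled OA-plus-others estimate and that this estimate cannot exist. No section promises one; Planned Analysis speaks only of examining trends and effect sizes. Even under replacement, allocation is by practice and not by item version, so arms can be compared within each version and combined with version as a stratum. Bothersomeness is described without any OA rewording and is collected from all patients before the consultation and at follow-up.
- A reader might measure the loss by the standard error of an overall mean: √(180/120) = 1.22, or 22% larger without clustering. With 10 equal practices and variance proportional to (1 + (m − 1)ρ)/(10m), for m = 12 against 18, the ratio is 1.19 at an assumed ICC of 0.01 and 1.12 at 0.05. The arithmetic is right, but the protocol wants the SD and ICC, not that mean. Recruitment caps also fix OA at a third of the sample, whereas the protocol expects about 18 others for each OA patient.
- A reader might object to the two-week look-back, since a late form would be anchored after the consultation. Follow-up is set at two weeks, no lateness figure is given, and timing feasibility is already a study outcome. The remark in Timing and Modality that outcomes on symptom perception are "possibly also those outcomes capturing symptom perception, are likely to be immediate" is hedged by its first word and explains the post-consultation measures. Re-anchoring the wording would be a preference, not a correction.

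**Conclusion.** The inconsistency is real and worth correcting. One section offers symptom change on overall symptoms as a shared candidate primary outcome; another gives OA patients a knee or hip version; Table 2 provides for a single item. If the OA version replaces the generic one, as the text most naturally reads, up to 60 of 180 patients (33%) do not answer the generic item. Its feasibility in OA patients is then untested, and its SD and ICC come from at most 120 patients, or 96 at 80% completion, all outside the OA group.

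This rests on two assumptions: that replacement is what is meant, and that recruitment reaches its caps. If OA patients are in fact meant to answer both items, only the wording and Table 2 are at fault. In either case, estimates within each item version and the bothersomeness candidate are unaffected.

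**What to change.** - Have all patients, OA and others, complete the identical overall symptom change item at follow-up.
- Have OA patients complete the knee or hip item in addition, labelled as the target-joint global assessment.
- Show the knee or hip item as a separate OA row in Table 2, and keep the existing row for the generic item.
- State in Measures Completed by All Participants that the generic item is the all-consulter candidate primary outcome, and in Measures Completed by the OA Group that the joint-specific item is added and does not replace it.

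The cost is one extra item at follow-up for up to 60 patients, one table row and two sentences. The adapted wording of the items, including the two-week look-back, can stay as it is.

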### Planned Analysis

Data will be downloaded from LifeGuide and Qualtrics, cleaned, and imported into SPSS/STATS for analysis.

Scale scores on all outcome and process measures as appropriate will be computed following published guidelines.

We will examine the psychometric properties of all bespoke items and the TEX-Q (previously validated in German but not English) before included them in analyses.

Trends and effect sizes on process measures and patient reported outcomes will be examined.

Recruitment rates, attrition rates, and intervention usage data from LifeGuide will be examined.

We will explore how to analyse the films of baseline and post-randomisation consultations. This will include an exploration of how to sample films for analysis; how to code them reliably for the presence of techniques trained in EMPathicO using a simple checklist to be devised when the intervention is finalised; and how to explore for indicative evidence of PCP behaviour change following intervention.

We will analyse qualitative data descriptively using content analysis, possible supplemented by thematic analysis if time allows. Qualitative data from PCPs and patients will be analysed to suggest improvements to EMPathicO and to explore potential mechanisms of action that may or may not be consistent with the logic model. Qualitative data from PCPs and practice staff and patients and researchers' field notes will be analysed to suggest improvements to trial procedures. Qualitative data from patients will be analysed to inform choice of process and outcome measures for the full trial. Multiple researchers will be involved in the qualitative analysis to guard against idiosyncratic or overly-selective coding. NVivo will be used to facilitate coding and ensure an audit trail of the analysis is maintained.

The full trial draft power calculation is conservatively based on systematic reviews suggesting a standardized effect size of 0.25 for optimising expectations; sample size calculations will be further refined by calculating completion rates, ICCs, and standard deviations here.

The intervention and full trial design will be finalised after considering both quantitative and qualitative findings.

Table 3 summarises the trial objectives and maps them to data collected and the planned analyses.

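### As described, the pain-medication form lists only medicines in use at the two-week follow-up, so one stopped since the consultation may go unrecorded while one newly started is recorded

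*Protocol*

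**What the plan says.** The purpose is set out in the Protocol under Measures Completed by the OA Group: "Changes in osteoarthritis pain medication will be assessed using a bespoke Osteoarthritis Pain Medication Questionnaire". The same paragraph describes the content. "This instrument asks patients to list all the osteoarthritis pain medications they are using", with tablets, other medicines, gels and creams all included, and patients are asked "to rate whether and how, since starting the study, they have changed the amount that they use".

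Table 2 names the construct as a change in pain medication, gives the "Bespoke Osteoarthritis Pain Medication Questionnaire" five items, and schedules it at follow-up only, with dashes at every earlier time-point. Under Timing and Modality, "The follow-up time-point is two weeks after the index consultation".

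The items, response options and scoring of the form are not reproduced. On scoring, Planned Analysis offers only the general statement "Scale scores on all outcome and process measures as appropriate will be computed following published guidelines".

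**The concern.** The two halves of the instrument are anchored to different times. The list is anchored to what the patient takes at week two. The change to be rated runs from the start of the study. With no list from the start, the week-two list alone decides which medicines are asked about, and a stopped medicine has by definition left it.

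Stopping is the complete form of reduction, so a change measure that may miss it is weak at one end of its range, and the weakness is one-sided because starts remain visible. Stopping is also plausible in this population: the protocol's Introduction reports that many patients give up opioids and intra-articular corticosteroids after some weeks, although that yields no two-week rate.

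Two uses of the data are at stake. The pain rating scale and the HOOS/KOOS are collected at the same follow-up, and reading them sensibly requires knowing whether analgesic use has gone up or down. Aim 3 of the trial is to finalise outcome measures, so a gap left in the form now could pass into the definitive trial.

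**Working it through.** No figure in the protocol bears on this point and there is nothing to recompute. The check is textual.

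**Step 1: what is listed.** Medicines in present use, at the time the form is completed (Measures Completed by the OA Group).

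**Step 2: what is rated.** Change since starting the study in the amount the patient uses. The natural reading is that this refers to the listed medicines, but the text does not say whether the rating is made per medicine or once overall.

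**Step 3: when.** Follow-up only (Table 2), two weeks after the consultation (Timing and Modality).

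**Step 4: is there an earlier list elsewhere?**
- Table 2 has no other medication measure.
- The clinical record form (Confirming Eligibility: CRF) holds the study identifier, the OA diagnosis, an age band and the practitioner's view on ability to consent or complete questionnaires. It has no medication item.
- Medical notes are not used in this trial. Under Outcomes: "While in a future definitive trial we would want to collect data on healthcare utilisation, for example from a notes review".

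So no earlier list is described.

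**Step 5: apply the description to hypothetical patients, rating per listed medicine.**

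| Patient | At the consultation | By week two | What the form holds |
|---|---|---|---|
| A | Two OA pain medicines | One stopped, one unchanged | The remaining medicine, rated unchanged; the stopped one unrated |
| B | One | Stopped | Empty list |
| C | None | One started | The new medicine, listed and rated |
| D | None | None | Empty list |
| E | One | Replaced by another | The new medicine only; the old one unrated |

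C's start is visible. The stops of A, B and E are not. B and D return the same record although B made the largest possible reduction and D made no change.

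**Step 6: does the alternative reading remove the problem?** If patients give one overall rating, A could report using less and the stop would be partly captured. B would still have an empty list, and the description does not say what such a patient should answer. The gap is smaller on this reading but does not close.

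**The case against.** The strongest reply is that one descriptive sentence is not the questionnaire. Five items exist and none is shown. The rating of whether and how use changed could include a 'stopped' answer, and the design drew on a validated medication-change questionnaire whose handling of stops cannot be seen from here. This stands as a limit on the claim: the point concerns the form as described. It does not fully answer it, because a patient told to list what they are using has no described prompt to enter a medicine they no longer use, so a 'stopped' answer might never be reached.

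A second reply is that the form is under test. Planned Analysis states "We will examine the psychometric properties of all bespoke items" before they enter analyses, and patient interviews cover questionnaire relevance. That is fair, and it lowers the severity. Yet psychometric checks work on recorded answers, and an unlisted medicine leaves none; interviews might reveal the gap only by chance.

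A third reply is that little depends on the measure here. The Randomization section says effectiveness is not being assessed, and the candidate primary outcomes are the HOOS-12/KOOS-12, symptom change and symptom bothersomeness. This stands in full.

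**Conclusion.** The point holds in limited form. The listing rule in the protocol, combined with a single administration and no earlier list, means that discontinuation may be missed while starts are captured, and that an empty list is ambiguous. This rests on the protocol's description being faithful to the form, and it is clearest if change is rated per listed medicine.

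Three stronger conclusions might be inferred and are not supported:
- *That a stopped medicine is scored as no change.* No scoring rule is given for this form. The stopped medicine is unrated, and a patient who stopped everything has a missing or ambiguous record, which is not the same as a score of no change.
- *That the form can never show a stop.* Its items and response options are not shown.
- *That the error has a known size.* One could assume that 5% to 20% of the OA patients stop a medicine and multiply by 60, giving 60 × 0.05 = 3 to 60 × 0.20 = 12 patients. The protocol supplies no such rate, 60 is a ceiling on OA recruitment, and calling those patients misclassified again presumes a scoring rule.

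Severity is low. This is a secondary measure in a feasibility trial, and the progression criteria concern recruitment and practitioner log-on.

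**What to change.** Have the form ask for every OA pain medicine used at any time since starting the study, explicitly including the day of the index consultation. For each one, include 'started' and 'stopped' among the change answers and treat 'stopped' as a reduction. Add a response that separates no OA pain medicine used from all such medicines stopped. Amend the description under Measures Completed by the OA Group to match. If the existing form already works this way, only that description needs correcting.

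The same edit is a convenient moment to reconcile a separate mismatch: the text places the form among the OA group's measures, whereas Table 2 marks it for all patients.

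The cost is rewording one bespoke form, at most an extra line or two for the patient, and some reliance on recall over two weeks. No time-point is added.
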